## Abstract

**Background:**

Atopic dermatitis (AD) is a chronic inflammatory skin condition that presents a significant disease burden, being the most prevalent non-fatal skin disease globally. While topical treatments play a vital role in managing mild-to-moderate AD, existing therapies often offer limited efficacy or have undesirable side effects. Fuzhiqing ointment, formulated from 15 traditional Chinese herbs, has demonstrated promising effects in anti-inflammatory, antipruritic, and anti-infective properties. Despite its widespread use in clinical practice, particularly for treating itching skin diseases, high-quality clinical evidence supporting its effectiveness in AD remains scarce. This trial seeks to address this gap by evaluating the clinical efficacy of Fuzhiqing ointment in managing mild-to-moderate AD, providing critical evidence for its potential integration into mainstream dermatologic care.

**Objectives:**

This multicenter, randomized, double-blind, placebo-controlled clinical trial aims to assess the efficacy of Fuzhiqing ointment in alleviating the symptoms of mild-to-moderate AD. We hypothesize that the inclusion of Fuzhiqing ointment in the treatment regimen will lead to a significant improvement in clinical outcomes compared to placebo, offering an innovative therapeutic approach in the AD treatment landscape.

**Methods and analysis:**

A total of 210 patients with mild-to-moderate AD will be recruited from 10 hospitals across China between September 2025 and February 2026. Participants will be randomly assigned in a 2:1 ratio to receive either the treatment (urea vitamin E cream combined with Fuzhiqing ointment; *n* = 140) or the control (urea vitamin E cream combined with placebo Fuzhiqing ointment; *n* = 70). Both groups will apply the treatments twice daily for 2 weeks, followed by a 4-week observational follow-up period. The primary outcome will be the proportion of patients achieving ≥50% improvement in the Eczema Area and Severity Index (EASI) score at week 2 (EASI_50_). Secondary outcomes will include changes in the EASI, Numerical Rating Scale (NRS), Investigator’s Global Assessment (IGA), Dermatology Life Quality Index (DLQI), and Atopic Dermatitis Control Tool (ADCT) at weeks 1 and 2, as well as the EASI, NRS, and adverse events at week 6. Statistical analyses will be performed using SAS 9.4, with significance defined at a two-tailed *α* level of 0.05.

**Results:**

In this study, ethics approval was obtained in December 2024 and registered in Chinese Clinical Trial Registry in January 2025. Participant recruitment was commenced in February 2025 and is expected to be completed by February 2026. Data analysis will be initiated in May 2026, and the preliminary trial results are expected to be submitted for peer-reviewed publication in December 2026.

**Clinical trial registration:**

https://www.chictr.org.cn/, Identifier ChiCTR2500095971.

## Introduction

Atopic dermatitis (AD) is a chronic, recurrent, inflammatory skin disease characterized by severe itching, dry skin, and typical eczematous lesions (1). Its pathogenesis is complex, involving skin barrier dysfunction, immune dysregulation, environmental factors, and genetic susceptibility. AD is associated with a significant disease burden and represents the highest burden among all non-fatal skin diseases (2). Beyond cutaneous manifestations, AD profoundly impacts patients’ quality of life, contributing to sleep disturbances, cognitive impairments and heightened risks of anxiety and depression (3).

In recent years, numerous treatments for AD have been developed, including emollients, corticosteroids, calcineurin inhibitors, antihistamines and biologics (4–6). Topical treatment is crucial for the long-term management of AD, particularly in those with mild-to-moderate symptoms. However, current therapeutic options have limitations, including the potential side effects of long-term potent corticosteroid use, inadequate efficacy or frequent recurrence in some patients, and concerns regarding the applicability and safety of systemic therapies (7–9). Therefore, developing safe, effective, and easily manageable new topical treatment options is still important clinical need.

Traditional Chinese Medicine (TCM) has been increasingly recognized for its therapeutic potential in treating mild-to-moderate AD (10–15). One such formulation, Fuzhiqing ointment, contains a combination of 15 Chinese medicinal herbs, including Tinospora root, Rhubarb, Golden cypress, *Ardisia crenata*, Chinese violet, Wild chrysanthemum, Hemsleya amabilis, *Sophora flavescens*, Paris polyphylla, Airpotato yam, Turmeric, *Sanguisorba officinalis*, Kuding tea, Borneol, and Menthol. Each herb in the formulation plays a distinct role in addressing the underlying pathophysiology of AD. For instance, *Sophora flavescens* has known anti-inflammatory and antibacterial properties, which help reduce the inflammatory responses that characterize AD. Turmeric is recognized for its potent antioxidant and anti-inflammatory effects, supporting skin healing and reducing irritation. Other herbs, such as *Sanguisorba officinalis* and Paris polyphylla, contribute to enhancing skin barrier function by promoting moisture retention and skin regeneration. Existing research has demonstrated that Fuzhiqing ointment exerts anti-inflammatory, antipruritic, and anti-infective effects, which contribute to its therapeutic efficacy in managing AD symptoms. The ointment works by replenishing skin moisture and lipids, thereby aiding the restoration of the skin’s physical barrier. This action effectively reduces transepidermal water loss and helps maintain the skin’s physiological acid–base balance. Additionally, it inhibits pathogen proliferation, thereby decreasing the skin’s sensitivity to external stimuli such as allergens and irritants. The absence of hormonal components in the formulation also makes Fuzhiqing ointment a safer alternative for patients seeking long-term relief from AD, as it minimizes the risk of side effects typically associated with hormone-based treatments.

Although Fuzhiqing ointment is commonly used in clinical practice to treat itching skin diseases such as eczema and AD. However, there is currently a lack of high-quality clinical trial evidence to support its clinical efficacy in the treatment of mild-to-moderate AD. Therefore, we implement this multicenter, randomized, double-blind, placebo-controlled clinical trial to evaluate the efficacy of Fuzhiqing ointment in patients with mild-to-moderate AD. We hypothesize that Fuzhiqing ointment will effectively alleviate symptoms in patients with mild-to-moderate AD, and findings in this study will potentially offering a new treatment option for patients with AD patients.

## Methods and analysis

### Study design

This study is a multicenter, randomized, double-blind, placebo-controlled trial to evaluate the efficacy of Fuzhiqing ointment in treating mild-to-moderate AD. The study design adheres to the SPIRIT (Standard Protocol Items: Recommendations for Interventional Trials) statement (16). A total of 210 patients with mild-to-moderate AD will be recruited in 10 hospitals between September 2025 and February 2026. Participating sites include Shanghai Skin Disease Hospital, Yueyang Hospital of Integrated Traditional Chinese and Western Medicine affiliated to Shanghai University of Traditional Chinese Medicine, China-Japan Friendship Hospital, Hangzhou Third People’s Hospital, Chongqing Traditional Chinese Medicine Hospital, The Second Affiliated Hospital of Xi’an Jiaotong University, Beijing Hospital of Traditional Chinese Medicine, Guangdong Provincial Hospital of Chinese Medicine, Peking University Third Hospital and Hubei Provincial Hospital of Traditional Chinese Medicine. A total of 210 patients with mild-to-moderate AD will be randomly allocated in a 2:1 ratio to the treatment group (urea vitamin E cream and Fuzhiqing ointment; *n* = 140) or the control group (urea vitamin E cream and placebo Fuzhiqing ointment; *n* = 70). Each patient in both groups will receive two treatment sessions per day for 2 weeks, followed by a 4-week follow-up period. The study flowchart is presented in Figure 1.

**Figure 1 fig1:**
[figure not shown]
Clinical trial flowchart.

### Inclusion criteria

The inclusion criteria for mild-to-moderate AD patients include: (1) patients diagnosed with mild-to-moderate AD according to the Williams criteria [guideline for primary care of atopic dermatitis, 2022 edition (17)], (2) the skin lesions accounted for less than 10% of the body surface area (BSA), (3) the skin lesions are mainly located in the limbs or trunk, (4) male or female patients aged 18–60 years, and (5) signed informed consent forms.

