### Outcomes

#### Primary outcome

The primary outcome indicator in this study is the EASI50 achievement rate at week 2. The EASI50 achievement rate is defined as the proportion of patients with mild-to-moderate AD who achieved ≥50% improvement in EASI score from baseline to week 2.

The EASI score includes the affected body surface area score (A) and clinical features score (B) of the head and neck, trunk, upper limbs, and lower limbs (19). (A) involves evaluating the percentage of affected body surface area (BSA) for each part. The percentage of affected BSA for each region is scored on a scale of 0–6: 0 (0%), 1 (<10%), 2 (10–19%), 3 (20–49%), 4 (50–69%), 5 (70–89%), and 6 (90–100%). (B) assesses four key clinical features, including erythema (E), edema/papules/infiltration (I), excoriation (Ex), and lichenification (L). Each feature is scored based on severity, ranging from 0 to 3 points (0 = none, 1 = mild, 2 = moderate, 3 = severe). The EASI score is calculated by multiplying the product of (A) and (B) with regional weighted coefficient (0.1–0.4) and then summing across all regions. The total score of EASI ranges from 0 to 72 points, with higher scores indicating greater severity. According to the EASI score, the skin lesion condition of AD patient is considered as mild (0–7 points), moderate (7–21 points), or severe (>21 points). In this study, the EASI score will be estimated at baseline (week 0), week 1, week 2, and week 6.

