### IGA

IGA is a validated 6-point ordinal scale enabling rapid clinical evaluation of disease severity (23). Dermatologists assess key features of skin lesion by using the following criteria: 0 = clear (no erythema), 1 = almost clear (minimal erythema; barely perceptible edema/papules), 2 = mild (mild erythema; palpable edema/papules), 3 = moderate (moderate erythema; evident edema/papules), 4 = severe (severe erythema; marked edema/papules), and 5 = very severe (confluent erythema with edema). IGA scores will be evaluated at baseline, week 1, and 2.

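### Entry has no lower severity limit and the protocol's scales disagree on where mild begins, so EASI50 can turn on one rating grade in patients near the floor

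*Protocol article*

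**What the plan says.** Under Inclusion criteria, the article admits "patients diagnosed with mild-to-moderate AD according to the Williams criteria", citing a 2022 primary-care guideline. The one measured lesion limit is that "the skin lesions accounted for less than 10% of the body surface area (BSA"), an upper limit on extent. Lesions must lie mainly on the limbs or trunk. Neither the inclusion nor the exclusion criteria give an EASI, IGA or NRS value.

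Under Primary outcome, EASI severity is banded as "mild (0–7 points), moderate (7–21 points), or severe (>21 points"). Each of four signs is graded "ranging from 0 to 3 points (0 = none, 1 = mild, 2 = moderate, 3 = severe"), and the area score in each region runs "0 (0%), 1 (<10%), 2 (10–19%), 3 (20–49%), 4 (50–69%), 5 (70–89%), and 6 (90–100%)." The score is the sum over regions of weight × area score × sign sum, with weights from 0.1 to 0.4. The endpoint is the proportion of patients whose EASI falls by at least 50% from baseline to week 2.

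Under IGA, the lowest grades are "0 = clear (no erythema") and "1 = almost clear (minimal erythema; barely perceptible edema/papules), 2 = mild (mild erythema; palpable edema/papules").

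Table 2 has both EASI and IGA scored at Visit 1. Statistical analysis compares categorical variables by chi-square or Fisher's exact test.

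**The concern.** A relative endpoint needs a baseline high enough for a 50% fall to mean something. Here nothing numerical keeps the baseline off the floor, and the two scales that could define the lower edge of mild do not agree. The EASI bands count a score of 0 as mild. On IGA the corresponding bottom grades are clear and almost clear, both below mild. The text does not say which scale, if either, the investigators at ten hospitals should use at entry.

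Two things are at stake. First, near the floor the primary endpoint can record rater scatter as response, in both arms alike, which pulls the arms together. Second, a patient at IGA 1 is not mild on the protocol's own IGA, yet could count towards a conclusion about mild-to-moderate disease.

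**Working it through.** **Inputs from the article.** EASI formula, sign grades and area scores (Primary outcome); EASI50 rates of 60% and 30%, two-sided α 0.05, power 80%, 116 + 58 patients, enlarged to 140 + 70 (Sample size). Taking off the stated 10% dropout gives 140 × 0.9 = 126 and 70 × 0.9 = 63 evaluable.

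**The plan's own figure.** A pooled two-proportion z test at 60% vs 30%, 2:1, 80% power needs 64 + 32, not 116 + 58. The stated 116 + 58 has 97.0% power and 126 + 63 has 98.0%. That mismatch is a separate matter; it is used here only as the starting power.

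**Step 1: what one grade does.** With one affected region, EASI = w·A·B (weight, area score, sign sum). Losing one grade on one sign is a fall of 1/B, and w and A cancel.

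| Sign sum B | EASI at A = 1, w = 0.1 to 0.4 | Fall from one grade | EASI50 met? |
|---|---|---|---|
| 1 | 0.1 to 0.4 | 100% | yes |
| 2 | 0.2 to 0.8 | 50% | yes |
| 3 | 0.3 to 1.2 | 33% | no |
| 4 | 0.4 to 1.6 | 25% | no |

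In addition, an area score moving from 2 to 1 in the only affected region (for example 10% to 9% of that region) is a 50% fall at any sign sum, with all signs unchanged. At a baseline of 0 the percentage is undefined.

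**Step 2: false response with no true change.** Assumption, not in the article: at week 2 each sign is rated one grade off with probability q = 0.2 to 0.4, half up and half down, and a grade of 0 cannot go lower. Take A = 1 and w = 0.4.

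- One grade-1 sign (EASI 0.4): (q/2)(1 − q/2)³ = 0.1 × 0.729 = 7.3% at q = 0.2, and 0.2 × 0.512 = 10.2% at q = 0.4.
- Two grade-1 signs (EASI 0.8): 2(q/2)(1 − q)(1 − q/2)² + (q/2)²[1 − (q/2)²] = 0.1296 + 0.0099 = 14.0% at q = 0.2, and 0.1536 + 0.0384 = 19.2% at q = 0.4.
- Full enumeration gives 1% to 11% at EASI 1.2 to 1.6, depending on how the signs are spread, and 0 at EASI 3.6 (signs 3, 2, 2, 2).

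**Step 3: effect on power.** Let a share f of patients be near the floor and misclassified at 19% in both directions, so m = 0.19f. Only false response was derived in Step 2; applying the same rate to missed response is an added, pessimistic assumption. The rates become 0.60 − 0.2m and 0.30 + 0.4m, and their weighted mean stays at 0.5. Power = Φ[(Δ − 1.96·s0)/s1], with s0 = √[0.25(1/63 + 1/126)] = 0.0772 and s1 the unpooled standard error. At f = 50%: (0.243 − 0.1512)/0.0741 = 1.24, giving 89%.

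| Share f | m | Rates | Difference (points) | Power |
|---|---|---|---|---|
| 0 | 0 | 60.0% vs 30.0% | 30.0 | 98.0% |
| 10% | 1.9% | 59.6% vs 30.8% | 28.9 | 97.1% |
| 20% | 3.8% | 59.2% vs 31.5% | 27.7 | 95.8% |
| 30% | 5.7% | 58.9% vs 32.3% | 26.6 | 94.1% |
| 50% | 9.5% | 58.1% vs 33.8% | 24.3 | 89.2% |

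With false response only (rates 0.60 + 0.4m and 0.30 + 0.7m), power over the same shares is 98%, 97%, 96% and 95%.

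**Step 4: what would take power below 80%.** With misclassification in both directions, power is 80.7% at m = 14.0% and 79.6% at m = 14.5%. At 19% this needs about 0.14/0.19 = 74% of all patients near the floor. If rating error also affects the baseline score, false response rises to 28–33% at EASI 0.4 and 15–22% at EASI 0.8. Even at 33%, the break-even share is about 0.14/0.33 = 42% of the trial with a single grade-1 sign.

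**The case against.** Much of the opposing case stands.

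- A reader might infer that entry has no measured limit at all. It has one: the cap on body surface area. What is absent is a lower limit.
- A reader might infer that near-clear patients will be enrolled. The article does not show that. Criterion 1 requires mild-to-moderate disease, criteria 2 and 3 presuppose visible lesions, and the cited guideline, which is not at hand, may grade severity. A patient with EASI 0 is an unlikely entrant. The point is that the text leaves the lower edge open and inconsistently labelled.
- EASI and IGA are different instruments and neither is stated as an entry rule, so the disagreement admits nobody by itself. It does leave the label without a usable definition.
- A reader might infer a serious loss of power, for example 73% if misclassification averaged 17% in both directions over all patients. The calculation does not support that average: with week-2 error only, nearly the whole trial would have to sit near EASI 0.8 with about 40% of signs misrated.
- The 60% and 30% rates are taken from previous evidence. If they were observed rates, they already contain some rating error, and the losses above partly count it twice.
- A reader might infer bias. Allocation is random, and patients, investigators and assessors are blinded, so the scatter is non-differential: it dilutes, and favours neither arm.

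Baseline adjustment is often left to an analysis plan. Here, however, the article names an unadjusted test for categorical outcomes, so that choice can fairly be questioned.

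**Conclusion.** The point holds in a limited form. Entry rests on a severity label with a ceiling on extent and no floor, the protocol's scales place the start of mild differently, and EASI 7 belongs to two bands. By the protocol's own formula, a single affected region with sign sum 1 or 2 reaches EASI50 on a one-grade change.

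The likely cost is modest: at 19% misclassification in both directions, power at 126/63 stays at about 89% to 97% for near-floor shares of 50% down to 10%, above the stated 80% target. This rests on assumed rating error at week 2 only, on 60% vs 30% being free of that error, and on a near-floor share that the article does not give. The stronger reason to act is interpretation: the text does not establish that everyone enrolled has mild or moderate disease on the protocol's own scales.

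**What to change.** - **Entry.** Reconcile Inclusion criteria, Primary outcome and IGA by stating which Visit 1 score defines mild-to-moderate for patients still to be enrolled, for example the protocol's own IGA grades 2 and 3.
- **Bands.** Correct the EASI bands so that mild does not start at 0 and 7 falls in one band only.
- **Analysis.** Keep every randomised patient in the ITT set. Replace the unadjusted chi-square test of EASI50 with a model adjusted for baseline EASI, and state how a baseline of 0 is counted.
- **Sensitivity.** Prespecify an analysis without patients whose baseline is such that a one-grade change in one sign, or an area score moving from 2 to 1, gives a 50% fall by itself. A floor on the sign sum alone would leave the area route open. A move from area score 1 to 0 means that the region has cleared and should not count for this purpose. The set depends on baseline data only, so the comparison within it remains randomised.

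**Cost.** No new assessment is needed, since both scores are already taken at Visit 1. The eligible pool becomes slightly smaller. The article has recruitment ending by February 2026, so an amendment during recruitment changes the entry criteria part-way and must be reported. If it is too late for that, the band correction and the analysis changes can still be made before the analysis planned for May 2026.

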### Exclusion criteria

The exclusion criteria include: (1) patients who are pregnant, breastfeeding, or planning to become pregnant; (2) patients who have received AD system treatment within the past 3 months or have received local treatment or phototherapy within the past 2 weeks; (3) patients who are allergic to the intervention drug components; (4) patients with systemic diseases or active skin diseases that may affect the evaluation; (5) patients with scars, tattoos, birthmarks, and sunspots that affect the skin lesion evaluation; (6) patients who participated in other clinical trials within a month; and (7) patients with communication barriers who are unable to independently complete the case report form (CRF).

### Sample size

The sample size was calculated based on the EASI50 achievement rate at week 2, which was defined as the proportion of patients who achieved ≥50% improvement in Eczema Area and Severity Index (EASI) score from baseline to week 2. According to previous evidence, we assume that the EASI50 achievement rate at week 2 was 60% in the treatment group and 30% in the control group (18). The sample size calculation for a 2:1 randomization design performed in PASS 15.0 (NCSS Statistical Software) indicates that 116 patients in the treatment group and 58 patients in the control group need to recruit with a 2-tailed *α* level of 0.05 and a statistical power of 80%. Considering a dropout rate of 10 and 10% multicenter effect, the final enrollment targets are 140 patients in the treatment group and 70 patients in the control group.

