### Statistical analysis

In this study, analysis will be performed by applying SAS 9.4 statistical package. Normally distributed quantitative variables will be summarized as mean and standard deviation (SD), while those with skewed distributions will be presented as median and interquartile range (IQR). The Student *t*-test will be used for inter-group comparison of quantitative variables with normal distribution, while the Wilcoxon rank-sum test will be employed for quantitative data with skewed distribution. The repeated measurement data will be analyzed by repeated measure analysis of variance. Categorical variables will be reported as frequencies and proportions (%), with group differences assessed using chi-square tests or Fisher’s exact tests. In this study, data analysis will adhere to the intention-to-treat (ITT) principle, including all randomized patients regardless of protocol adherence or study completion (25). Missing data will be handled under the missing-at-random assumption using sequential regression multiple imputation, which imputes missing values through regression models for each variable conditional on the other variables (26). Additionally, data analysis will be conducted on both the full analysis set (FAS) and the per-protocol set (PPS), and a *p*-value less than 0.05 (two tailed) is considered as statistically significant.

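### The sample size of 116 + 58 does not follow from the stated inputs: 60% vs 30% at 80% power needs about 64 + 32, and 116 + 58 gives about 97% power

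*Protocol article*

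**What the plan says.** The Sample size section of the protocol article bases the calculation on the primary outcome and gives every input needed to repeat it:

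- Response rates: "we assume that the EASI50 achievement rate at week 2 was 60% in the treatment group and 30% in the control group".
- Allocation and software: "The sample size calculation for a 2:1 randomization design performed in PASS 15.0".
- Error rates: "with a 2-tailed *α* level of 0.05 and a statistical power of 80" percent.
- Result: the calculation "indicates that 116 patients in the treatment group and 58 patients in the control group need to recruit with a 2-tailed" alpha of 0.05, that is, 174 patients before any allowance.
- Allowances: "Considering a dropout rate of 10 and 10% multicenter effect, the final enrollment targets are 140 patients in the treatment group and 70 patients" as controls.

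The Statistical analysis section compares categorical variables between groups "with group differences assessed using chi-square tests or Fisher’s exact tests". The section states no non-inferiority margin, multiplicity adjustment, intracluster correlation or other design effect that would raise the number before the allowances.

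**The concern.** A 30-point difference around a 50% average response is large, and 174 patients is many for 80% power. If the stated inputs do not produce the stated numbers, something in the paragraph is misreported.

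This paragraph is the trial's only statement of the effect it is sized to detect. If the rates and patient numbers are right, the power is about 97%. If the power and patient numbers are right, the target was a difference of about 22 points. If the rates and power are right, the stated requirement is about 1.8 times what is needed (174/96), which bears on the justification for the number enrolled, including those on placebo. These are three different designs. A reader who later sees a 20-point difference could not say whether it fell well short of the planned effect or close to it.

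**Working it through.** **Inputs (Sample size section).** Control rate p2 = 0.30, treatment rate p1 = 0.60, difference 0.30, ratio 2:1, two-sided alpha 0.05 (z = 1.960), power 80% (z = 0.8416). The weighted mean rate is (0.30 + 2 × 0.60)/3 = 0.50.

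**1. Attempt to reproduce 58 control patients, pooled variance.**

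n(control) = [1.960 × √(1.5 × 0.5 × 0.5) + 0.8416 × √(0.3 × 0.7 + 0.6 × 0.4/2)]² / 0.30²

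= [1.2002 + 0.4835]² / 0.09 = 31.5

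This rounds up to 32 control and 64 treatment patients, 96 in all. It does not reproduce 58.

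**2. Other common methods, with the same inputs.**

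| Method | Control | Treatment | Total |
|---|---|---|---|
| Pooled, two-sided, 80% | 32 | 64 | 96 |
| Unpooled, two-sided, 80%: (1.960 + 0.8416)² × 0.33/0.09 = 28.8 | 29 | 58 | 87 |
| Arcsine, two-sided, 80% | 32 | 64 | 96 |
| Continuity-corrected, two-sided, 80% (36.3) | 37 | 74 | 111 |
| Pooled, two-sided, 90% | 42 | 84 | 126 |
| Continuity-corrected, two-sided, 90% | 47 | 94 | 141 |
| **Stated in the article, 80%** | **58** | **116** | **174** |

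By exact enumeration, Fisher's test already has 81% power at 70 + 35. No method gives 58 control patients at 80% power, or even at 90%. The pooled formula reaches 58 + 116 only when the power is set to 97%.

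**3. Power at the stated numbers for 60% vs 30%.**

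Pooled formula: z = (0.30 × √58 − 1.2002)/√0.33 = (2.2847 − 1.2002)/0.5745 = 1.888, so the power is 97.0%. Exact enumeration over the two binomial distributions gives:

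| Treatment + control | Chi-square | Fisher |
|---|---|---|
| 64 + 32 | 81.1% | 75.0% |
| 116 + 58 | 96.7% | 95.8% |
| 126 + 63 (210 less 10% dropout) | 97.7% | not computed |
| 140 + 70 | 98.7% | not computed |

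**4. Do the allowances explain the gap?** 116 × 1.2 = 139.2 and 58 × 1.2 = 69.6, which round up to 140 and 70. The two 10% allowances are therefore used in going from 174 to 210 and cannot also account for going from 96 to 174.

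**5. What difference fits 116 + 58 at 80% power?** Solving for the rates gives about 52% vs 30%, or 60% vs about 37.5%: a difference of about 22 points.

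**The case against.** Four points can be made for the plan.

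First, the number 58 does occur in a standard calculation: the unpooled formula gives 29 control and 58 treatment patients. If 58 was read as the control arm and doubled for 2:1 allocation, the result is exactly 116 + 58. All inputs may then have been entered correctly and only the output mistranscribed, in which case 80% was the true planning power. This is plausible but cannot be confirmed from the article. It limits the claim: the 80% is wrong given the other stated figures, and the article does not show which figure is at fault. It does not make the paragraph consistent.

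Second, the error is in the safe direction. On the stated assumptions the trial exceeds its stated power, and the test, the type I error and the analysis are untouched. The primary comparison does not depend on the planned difference. This stands, and it is why enrolment need not change. The planning statement is still false.

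Third, the Randomization section speaks of cluster randomization, and an unseen clustered calculation might have been used. Purely as an assumption, an intracluster correlation of 0.04 with 17.4 patients per hospital (174/10) inflates 96 to 96 × (1 + 16.4 × 0.04) = 159. A correlation of 0.05 with 21 per hospital gives 96 × (1 + 20 × 0.05) = 192. That range includes 174. But no such correlation is stated, patients are individually allocated in blocks, and the multicenter allowance is added separately after the 174. The text gives no support for this reading.

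Fourth, the intention-to-treat analysis with multiple imputation includes all 210 randomized patients, so 126 + 63 is not an analysis set the plan names. That is fair. The figure serves only to show power after the plan's own dropout allowance, and the finding does not rest on it.

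**Conclusion.** The point holds. With "EASI50 achievement rate at week 2 was 60% in the treatment group and 30% in the control group", 2:1 allocation, two-sided alpha 0.05 and "a statistical power of 80" percent, the requirement is 96 patients (111 with continuity correction), not 174. The stated 116 + 58 has about 97% power by the chi-square test and about 96% by Fisher's test, so the conclusion is the same under either test the plan names. It rests only on figures printed in the Sample size section and on the absence there of any further design effect. Which of the rates, the power and the patient numbers is misreported cannot be settled from the article. The consequence is a misstated design basis, not a loss of power.

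**What to change.** Recover the PASS 15.0 run and make the rates, the power and the patient numbers agree, naming the PASS procedure used. Depending on what the run shows:

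- **If 60% vs 30% was the assumption**, keep it and state that 116 + 58 evaluable patients give about 97% power. This sentence is true even if 116 + 58 arose from a transcription slip.
- **If other rates were entered**, state them; for example, 52% vs 30% matches 116 + 58 at 80% power.

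In either case, add the difference detectable with 80% power at the number of evaluable patients expected, so that readers can place the result. With 126 + 63, the pooled formula of the working gives about 51% against a control rate of 30%, a difference of about 21 points.

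The cost is the wording of one paragraph. Enrolment, randomization and the analysis stay as they are.
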